### **Malaria Case Tracker**

In order to assess the relationship between the treatments and malaria health outcomes, a case-control study will be used. The study population includes any child between the ages 6-24 months in July 2014 residing in the interventions areas. The study will begin following the first round of administration, and will continue until adequate numbers of cases and controls have been recruited (with a maximum of two months following the final round of distribution even though the estimated sample size may not be reached). The outcome of interest is confirmed clinical malaria (including severe cases) with cases defined as any child from the study population with a positive malaria test by either a Rapid Diagnostic Test (RDT) or microscopy. Controls are defined as children whose caregivers report they meet the following two inclusion criteria: 1.) no previous malaria symptoms (no fever in the last 4-weeks) and 2.) no care was sought for fever or other malaria symptoms in any health facilities since beginning of July 2014) will be recruited as controls. The assessed exposure is whether the children received SMC, SMC and nutrition products, or neither.

Starting directly after the first administration period, cases and controls will be recruited from health facilities. Information from both cases and controls will be collected through a short (about 30 minutes), pre-tested, malaria-case tracker that covers demographics (age, gender, ward of residence), malaria symptoms and severity, and nutrition indicators, and intervention exposure status (whether the child received SMC or nutrition products). Health care workers will be trained on case eligibility criteria and will collect the data on the child from the parent/guardian. Health care workers will be given a job aid that will assist them in classifying severe versus uncomplicated malaria based on the child's symptoms using the Nigerian National Policy. Data from the tracker will be aggregated by a trained health care

worker on a weekly basis and collected by CHAI staff through routine visits. Small facilitations fees will be given to health facilities for participation.

Assuming intervention coverage in the population of ~60% and a detectable odds-ratio of 0.6 (odds of receiving SMC + LNS among malaria cases compared to SMC alone), we would need to recruit 326 cases (aged 6 to 24 months) with a power of 90% and alpha of 5%. To increase power, controls will be selected at a ratio of 4 controls:1 case, meaning we will select 1,304 controls. Assuming approximately on average 5-6 confirmed cases of malaria, per health facility per month, recruitment will occur in 10 health facilities over a 6 months period August 2014-January 2015.

Case-control inclusion criteria are that the child must:

- 1.) Reside in the intervention catchment area
- 2.) Be 6-24 months of age at the start of the intervention (July 2014)
- 3.) Have a parent/guardian that provided informed consent (for parents/guardians who are between the ages of 12-18 they must provide informed assent and if their parent/guardian is nearby, this parent/guardian must also provide informed consent form)
- 4.) Must be eligible for SMC/LNS delivery (see eligibility criteria on pages 11-14)
- 5.) Cases must be parasitologically confirmed by either RDT or microscopy
- 6.) Controls must have had no previous malaria symptoms (no fever in the last 4-weeks) and no care was sought for fever or other malaria symptoms in any health facilities for them since beginning of July 2014)

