#### **Exclusion Criteria:**

- A child is 0-3 months of age or above 59 months of age.
- A child with severe acute illness or unable to take oral medication
- A child that has confirmed or suspected malaria. Confirmed malaria is defined as fever (body temperature  $\geq 37.5^{\circ}\text{C}$ ) or history of fever in the last 24 hours and parasitologically positive by Rapid Diagnostic Test (RDT) or microscopy; in the

absence of RDT and microscopy diagnosis, malaria diagnosis should be based on clinical signs and symptoms.

- An HIV-positive child and receiving co-trimoxazole.
- A child who has received a dose of either AQ or SP drug more recently than the past month.
- A child who is allergic to either drug (AQ or SP).

Children with severe acute illness or high fever that are not currently under a clinician's care will be referred to the nearest public health facility.

Table 5: Dosing guidelines for eligible children.

| Product and Dosing Information for SPAQ-CO |                                                                                                                                                                                                                                   |                          |                   |              |                   |              |                   |
|--------------------------------------------|-----------------------------------------------------------------------------------------------------------------------------------------------------------------------------------------------------------------------------------|--------------------------|-------------------|--------------|-------------------|--------------|-------------------|
|                                            | 
Brand Name and Formulation: SPAQ-CO
 
Co-blister of Sulfadoxine/pyrimethamine tablets + Amodiaquine tablets (SP+AQ)
 
Vendor: Guilin Pharmaceuticals
 
Catalog ID: 3.2.05.28.001.01.02
 |                          |                   |              |                   |              |                   |

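### The malaria outcome is called clinical, but a positive test alone makes a child a case; fever should be part of the case definition, and case and control rules should exclude each other

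*Protocol*

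**What the plan says.** Reduction in clinical malaria is one of the three primary outcomes in section 3 of the protocol. For the study that measures it, the Malaria Case Tracker section says "The outcome of interest is confirmed clinical malaria (including severe cases" and continues in the same sentence with "cases defined as any child from the study population with a positive malaria test by either a Rapid Diagnostic Test (RDT) or microscopy". Criterion 5 of the case-control inclusion list repeats the rule: "Cases must be parasitologically confirmed by either RDT or microscopy". Neither place mentions fever, fever history or symptoms.

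The SP-AQ exclusion criteria in section 4 contain the protocol's only definition of confirmed malaria. It begins "Confirmed malaria is defined as fever", sets the threshold at 37.5 °C, and goes on "or history of fever in the last 24 hours and parasitologically positive by Rapid Diagnostic Test (RDT) or microscopy".

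Controls are identified by report: "Controls are defined as children whose caregivers report they meet the following two inclusion criteria". The criteria concern symptoms and care-seeking: "Controls must have had no previous malaria symptoms (no fever in the last 4-weeks) and no care was sought for fever" or other malaria symptoms since the start of July 2014. No negative test is asked for.

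The source of controls is stated twice, differently. The introduction to section 5 takes them from the midline household survey. The Malaria Case Tracker section recruits both cases and controls at health facilities.

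**The concern.** The outcome label refers to illness, while the operative rule refers to parasitaemia. A child brought to a facility for another complaint, tested and found positive, counts as a case of clinical malaria without being ill from malaria.

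If LNS affects whether infection becomes illness and has little effect on carriage, such children carry no information on the SMC + LNS versus SMC contrast. Their presence moves the odds ratio toward 1.

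Cases are also defined by a test and controls by reported symptoms and care-seeking, so the two definitions do not exclude each other. Health workers are to be trained on the written eligibility criteria, so the wording decides who is recruited.

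**Working it through.** **Text comparison**

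| Rule | Fever or fever history | Positive test |
|---|---|---|
| Confirmed malaria (SP-AQ exclusion criteria) | required | required where a test is available |
| Case (Malaria Case Tracker, criterion 5) | not mentioned | required |
| Control (Malaria Case Tracker, criterion 6) | must be absent for 4 weeks; no care sought for fever or malaria symptoms since July 2014 | not mentioned |

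A child with a positive test, no fever for 4 weeks and no malaria-related care since July satisfies both the second and the third row. A child who meets the first row through fever plus a test cannot satisfy the third row at the time of recruitment.

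**Reproducing the plan's 326 cases**

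Inputs from the Malaria Case Tracker section: exposure 60%, odds ratio 0.6, power 90%, alpha 5%. The protocol does not state one- or two-sided; two-sided reproduces its figure.

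- Exposure in controls: p0 = 0.60, odds 1.5.
- Exposure in cases: p1 = 0.6 × 0.6 / (0.4 + 0.6 × 0.6) = 0.4737.
- Two-proportion formula, 1:1, pooled variance under the null, no continuity correction: n = [1.96 √(2 × 0.5368 × 0.4632) + 1.2816 √(0.4737 × 0.5263 + 0.60 × 0.40)]² / (0.60 − 0.4737)² ≈ 325.4, which rounds up to 326.
- Controls at 4:1: 326 × 4 = 1,304.

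The plan's figures are therefore correct on their own basis. The 326 is a 1:1 number, so the planned 4:1 design has about 98% power and not 90%.

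**Effect of incidental carriers**

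Let f be the share of cases who are carriers with the same exposure as controls. The protocol gives no value for f, so a range is assumed.

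- Exposure in recorded cases: pc = (1 − f) × 0.4737 + f × 0.60.
- Observed odds ratio: [pc / (1 − pc)] / 1.5.
- Power: same two-proportion method, two-sided 5%, 326 cases.

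| f | pc | Observed OR | Power, 1,304 controls (planned) | Power, 326 controls (basis of the 326) |
|---|---|---|---|---|
| 0 | 0.4737 | 0.60 | 98% | 90% |
| 10% | 0.4863 | 0.63 | 96% | 83% |
| 20% | 0.4989 | 0.66 | 91% | 74% |
| 30% | 0.5116 | 0.70 | 82% | 62% |

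The extra controls protect power. They do nothing for the attenuated odds ratio.

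**Interaction with criterion 4**

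Criterion 4 requires a case to be eligible for SMC/LNS delivery, and the SP-AQ criteria exclude a child with confirmed or suspected malaria. The protocol does not say when criterion 4 is assessed. If it is assessed at case detection, a febrile test-positive child is ineligible. Adding fever to the case rule without settling this point could then leave no eligible cases.

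**The case against.** The outcome sentence does contain the word clinical, and the test clause can be read as explaining only what confirmed means. The context supports that reading. Section 5 says cases come from facilities because acute episodes are hard to find in household surveys, and staff grade severity from symptoms. No passage describes testing attenders who have no symptoms. This stands as a reason to expect few carriers. It does not supply a rule, because the wording that staff would apply admits any child with a positive test.

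The definition in the SP-AQ criteria was written to decide who receives SMC. It also allows diagnosis on clinical signs where no test is available, which criterion 5 does not. It is therefore fair to call it the protocol's only definition of confirmed malaria, but not its stated outcome definition.

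The overlap with controls is narrower than it first appears. If controls come from the midline survey, no testing of them is described, and an untested child does not meet the case rule at that point. Overlap at recruitment depends on the sentence that places control recruitment at facilities. Even there, a child brought in for any malaria symptom fails the control criteria.

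The tracker records symptoms and severity, so a later restriction of the cases is possible. No rule in the protocol calls for one.

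**Conclusion.** The point holds as an inconsistency in the definition of a primary outcome. The protocol names clinical malaria, defines a case by a test alone, and leaves the case and control rules able to overlap if controls are recruited at facilities.

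Its size is unknown. The odds ratios of 0.63, 0.66 and 0.70, and the planned-design power of 96%, 91% and 82%, rest on an assumed carrier share of 10% to 30% and on carriers having control-like exposure to SMC + LNS versus SMC. At 10% and 20%, power stays above the 90% target.

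A reader might infer more than the text supports:

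- **That the protocol chose to count carriers, or that a case must be afebrile.** It only fails to require fever.
- **That the planned study would drop to 62% power.** That figure belongs to a 1:1 design; 4:1 is planned.
- **That the same dilution applies to SMC versus neither treatment.** An antimalarial may itself change carriage, so the no-association assumption need not hold there.
- **That nutrition-related attendance biases the comparison between arms.** This is conceivable, but nothing in the protocol shows or sizes it.

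**What to change.** Three edits, all to the case-control section and its cross-references:

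1. In the Malaria Case Tracker text and criterion 5, define a case for the analysis as temperature of at least 37.5 °C or fever history within 24 hours, plus a positive RDT or microscopy. State that afebrile positives are neither cases nor controls and enter a sensitivity analysis only.
2. State that criterion 4 is assessed at the intervention round and not at case detection, so that the malaria exclusion for SMC does not remove the cases. This concerns eligibility for the case-control study only and leaves the SMC delivery criteria untouched.
3. Reconcile the source of controls between the introduction to section 5 (midline survey) and the Malaria Case Tracker section (facilities).

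The cost is small. The tracker already collects malaria symptoms; the form and training need to make temperature or 24-hour fever history explicit if they do not already. Some afebrile positives will no longer count toward the 326, so recruitment may take slightly longer. The sample size does not need to be recalculated for this change.

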## 5 Monitoring and Evaluation Methods

Table 7 presents the data collection methods used for evaluation of the performance metrics previously outlined in Table 3, and the target population. Estimating intervention treatment coverage will be assessed through the midline cross-sectional household survey. The impact of interventions on nutrition health outcomes will be assessed through the three repeated cross-sectional household surveys. The impact of interventions on malaria health outcomes will be assessed through a case-control study using a malaria tracker where cases will be recruited from health facilities and control from the midline household survey. Cases will be recruited from facilities due to the challenge of identifying sufficient numbers of acute malaria episodes via monthly household surveys. Focus Group Discussions (FGDs) will be used to provide context to the results. CHAI will contract a private data collection firm to carry out the household surveys, case control study, collection of health facility records, and completion of FGDs. CHAI will carry out the data analysis and provide CIFF the full clean datasets from the firm upon request to validate findings.

Table 7: The data collection methods used for evaluation of the performance metrics previously outlined in Table 3, and the target population.

| Data Collection Method                                              | Timeline      | Inclusion Age*                | Location                     | Indicators                         |
|---------------------------------------------------------------------|---------------|-------------------------------|------------------------------|------------------------------------|
| Baseline Household Survey                                           | July 2014     | 6-24 months                   | Community                    | Malnutrition                       |
| Midline Household Survey
Nutrition Module
SMC Coverage Module | November 2014 | 6-28 months
(3-63 months)^ | Community                    | Malnutrition
Treatment Coverage |
| Endline Household Survey                                            | May 2015      | 12-34 months                  | Community                    | Malnutrition
Prevalence         |
| Malaria Case Tracker                                                | Continuous    | 6-24 months in July 2014      | Health Facility
Community | Malaria Incidence                  |

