## **Evaluation Data Collection Procedures and Participant Recruitment**

### **Household Surveys**

In total, three household surveys will be conducted, a baseline in July of 2014 alongside the first administration, midline in November 2014 after Round 4 of administration, and a final survey in May 2015, six months post intervention. The baseline survey will provide baseline information on demographics, and nutrition indicators. The midline survey will provide an estimate of the intervention coverage and adherence to SMC in addition to the nutrition indicators. The final survey six months after the endline administration will determine if there is a long-term health impact in terms of the nutrition indicators. Each questionnaire will be a pre-tested, interviewer-administered questionnaire lasting about 45-60 minutes.

For each survey, 1,500 households with at least one child that meets the inclusion age outlined in Table 6 will be selected to participate in the survey (a minimum of 750 households in each intervention study arm: SMC and SMC + LNS). This sample size is powered to measure a 10% difference in the outcome indicator (intervention coverage or nutrition indicator is estimated at 50%, which is conservative and gives the largest sample size) between the two intervention areas with an alpha of 5% and a power of 90%, and a design effect of 1.5.

A multistage stratified sampling strategy will be used for household selection. The sampling frame for the survey will come from the national sampling frame, which lists all the Enumeration Area (EA) maps of the 2006 Population and Housing Census conducted by the National Population Commission. Assuming 25 households are interviewed per EA, EAs are needed to achieve the total target sample size – in other words 30 EAs in each intervention arm. To account for the unlikely event that a randomly chosen EA did not contain 25 eligible households, 20 additional EAs will be randomly selected per intervention arm, making a total of 100 EAs selected per survey round (50 EAs per intervention arm). The supplemental EAs will only be used if needed. Using the 2013 population projections of each ward, we will use a probability-proportional-to-size methodology to select an appropriate number of EAs within each ward.

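### Case-control exposure is undated: if controls come from the November survey, early malaria cases have been offered fewer rounds and treated-versus-neither is biased below 1

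*Protocol*

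**What the plan says.** - **Exposure.** The Malaria Case Tracker section of the Protocol states: "The assessed exposure is whether the children received SMC, SMC and nutrition products, or neither". Among the tracker's listed contents is "intervention exposure status (whether the child received SMC or nutrition products". Neither place gives a round, a date, a count of rounds or a reference time.
- **Cases.** The same section says that "recruitment will occur in 10 health facilities over a 6 months period August 2014-January 2015". SMC rounds are monthly from July to October.
- **Controls, first statement.** The opening of section 5 says that "cases will be recruited from health facilities and control from the midline household survey". The Household Surveys section dates that survey: "midline in November 2014 after Round 4 of administration". The Treatment Registers section fits this reading, because registers are collected after round 4 and help to build the sampling frame for controls.
- **Controls, second statement.** The Malaria Case Tracker section has both groups enrolled at health facilities as soon as the first round is over.
- **Question asked.** Q-3 (Table 1) asks about SMC treatment as well as the package, and H-3 (Table 2) lists three exposure groups, one of them untreated. The sample-size paragraph powers only SMC + LNS against SMC alone.

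**The concern.** Ever-treated status can only rise as rounds pass. A child who becomes a case in August has been offered one or two rounds, whereas a child first seen in November has been offered four. If both are classified by whether they ever received SMC, controls have had more chances to count as exposed. The odds of exposure are then lower in cases than in controls for a reason unrelated to malaria, and SMC looks protective. The contrast at stake is treated versus neither, which is part of a stated primary hypothesis and would inform state and national decisions.

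**Working it through.** **1. The plan's own figure.** Inputs from the sample-size paragraph: exposure 60%, odds ratio 0.6, power 90%, alpha 5% (taken as two-sided). Exposure in cases = 0.6 × 0.6 / (0.4 + 0.6 × 0.6) = 0.4737. The usual two-proportion formula with pooled variance, 1:1 and no continuity correction gives

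n = [1.960 × √(2 × 0.5368 × 0.4632) + 1.2816 × √(0.24 + 0.2493)]² / (0.6 − 0.4737)² = 326 cases,

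which matches. So 326 is the 1:1 number, and four controls per case raise power to 98.4%.

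**2. Model for the null.** Assume no drug effect. Let c be coverage per round and w the share of children never reached. After r rounds, P(ever treated) = (1 − w)(1 − (1 − c)^r). Controls are taken at r = 4. Cases are averaged over month of onset, and from November they too have r = 4. None of the following is in the Protocol:
- Case mix August to January of 25/25/20/15/10/5%.
- c = 0.6, which borrows the plan's population coverage figure as a per-round value.
- w = 0.1, chosen to sit near the 2013 pilot, where nearly 90% had at least one course.
- Rounds offered to August, September and October cases of 1, 2, 3 or of 2, 3, 4. The season is given as 15 July to 15 October, so both are possible.

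**3. Worked case, c = 0.6, w = 0.1.** Ever treated after rounds 1 to 4: 54.0%, 75.6%, 84.2%, 87.7%.
- Schedule 1, 2, 3: cases = 0.25 × 0.540 + 0.25 × 0.756 + 0.20 × 0.842 + 0.30 × 0.877 = 0.756. Null OR = (0.756/0.244) / (0.877/0.123) = 0.43.
- Schedule 2, 3, 4: cases = 0.25 × 0.756 + 0.25 × 0.842 + 0.50 × 0.877 = 0.838. Null OR = (0.838/0.162) / (0.877/0.123) = 0.73.

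**4. Chance of a significant protective result with no effect**, at 326 cases and 1,304 controls: Φ(|ln OR|/SE − 1.96), with SE² = 1/(326·p₁q₁) + 1/(1304·p₀q₀), where p₁ and p₀ are the ever-treated shares in cases and controls. For the second case above, SE² = 1/44.2 + 1/140.7, SE = 0.172, and Φ(0.320/0.172 − 1.96) = 46%.

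| Coverage assumption | Rounds offered, Aug/Sep/Oct cases | Cases ever treated | Controls ever treated | Null OR | False protective result |
|---|---|---|---|---|---|
| 60% per round, 10% never reached | 1, 2, 3 | 75.6% | 87.7% | 0.43 | about 100% |
| same | 2, 3, 4 | 83.8% | 87.7% | 0.73 | 46% |
| 90% per round, 8% never reached | 1, 2, 3 | 89.4% | 92.0% | 0.74 | 31% |
| same | 2, 3, 4 | 91.7% | 92.0% | 0.97 | 3% |
| Ever-coverage 80% rising linearly to 90% | 1, 2, 3 | 85.2% | 90.0% | 0.64 | 70% |
| 90% from round 1, no new children later | any | 90.0% | 90.0% | 1.00 | nominal |

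With equal case numbers each month, the first row becomes 0.54 and the second 0.80.

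**5. The powered contrast.** Among treated children, the SMC + LNS versus SMC odds ratio is the ratio of ever-treated shares (LNS area over SMC area) in cases, divided by the same ratio in controls. Equal coverage in the two areas gives 1.00. With per-round coverage 70% against 60% (w = 0.1, schedule 1, 2, 3) it is (0.805/0.756)/(0.893/0.877) = 1.05. With 70% against 50% it is (0.805/0.692)/(0.893/0.844) = 1.10.

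**6. After the fix.** If controls carry index dates with the same monthly mix as cases, and only rounds before that date count, their exposed share in the first row is also 75.6%. The null OR is 1.00, for any c and w.

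**The case against.** **Controls may not be November controls.** The Malaria Case Tracker section enrols them at facilities alongside cases. If so, both groups are offered the same rounds at the same time and the bias need not arise. This stands, and it makes the point conditional. The survey reading is better supported: section 5 states it outright, the register text fits it, and a control must be a child for whom "no care was sought for fever or other malaria symptoms in any health facilities since beginning of July 2014", which suits community children better than facility attenders. Even on the facility reading, nothing holds the 4:1 ratio month by month.

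**The 0.6 is a different contrast.** A reader might set the null odds ratios beside the detectable 0.6 and infer that the whole target effect could be an artefact. The Protocol does not support that: 0.6 refers to SMC + LNS against SMC alone, where the distortion is only 1.00 to 1.10.

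**The dates exist.** Treatment cards and registers carry them, midline coverage is measured by round, and an analysis plan could define a window. This stands in part. For facility cases the tracker is described only as recording whether treatment was received, and use of the card is mentioned only for the household survey. The source of controls is a protocol matter.

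**Other features might seem to push the same way.** A reader might infer that counting a July dose as exposure in January, or requiring controls to have sought no care, also lowers a null odds ratio. Neither does so by itself. Stale exposure leaves a null odds ratio unchanged and dilutes a real effect towards 1. The no-care rule has no established direction, since it could select families less engaged with services and less often treated.

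**Withheld treatment.** The SMC exclusions include "A child that has confirmed or suspected malaria", so a child passed over while ill could be referred to a facility and enter there as an untreated case. The route is real but unsized: a dose in any other round still counts as exposure. Case-control criterion 4 also requires eligibility for delivery, although read literally it would bar every case. It merits a sensitivity analysis only.

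**Conclusion.** The point holds conditionally. If controls come from the midline survey and exposure is ever-received, the odds ratio for SMC or SMC + LNS against neither is biased in the protective direction whenever later rounds reach new children. It was never above 1 in the scenarios run. The null value is about 0.43 to 0.73 with 60% per-round coverage, 10% never reached and a seasonal case mix. It is 0.64 if ever-coverage rises from 80% to 90%, close to 1 with very high early coverage, and 1.00 with no later recruits. The size rests on coverage growth and case timing that the Protocol does not give. Under facility enrolment from round 1 the bias need not arise, but nothing in the text secures that. The SMC + LNS versus SMC comparison is not materially affected.

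**What to change.** 1. Reconcile section 5, the Malaria Case Tracker section and the Treatment Registers section on where and when controls are recruited.
2. Record SP-AQ dose dates and LNS ration dates from the treatment card or the distributor's register, in the same way for cases and controls.
3. Define exposure as the rounds of SP-AQ (and LNS) received before an index date. For cases this is symptom onset or presentation. For controls it is a date drawn from the case dates, or controls are matched to cases on calendar month. Compare within index month. For a control interviewed in November, an index date cut off at interview loses no rounds, because rounds end in October.
4. Do not make a dose within one dosing cycle the main definition. With rounds ending in October, nearly all children would be unexposed from about mid-November. Time since last dose can be a secondary analysis.
5. As a sensitivity analysis, exclude cases whose card shows SMC was withheld for the same illness.

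The cost is revised wording, one date field on the tracker, and some missing dates where cards are lost, which the registers can partly fill. The 326 cases are unchanged. The date field should be in place before recruitment, because undated answers may not be recoverable later.

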### **Treatment Registers**

Each CDD will be provided a treatment register at training and will be instructed on how to fill in the register. Every child that receives a dose of SP-AQ or SP-AQ + LNS will need to be entered into the treatment register before administration. As part of their involvement in this study, they will be requested to record the name, age, sex, and contact details of each child that they administer treatment to. If they do not feel able to complete the treatment register, they will not be able to participate in administration. It is expected to take less than 1 minute per patient to fill out the register. Study staff will collect the books after administration round 4. The purpose of the treatment registers is to provide on-going data on the number of treatments administered and to whom in each intervention area and assist with the development of the sampling frame for the control portion of the case-control study.

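### The protocol gives contradictory places and times for recruiting the H-3 controls, and lets a register of dosed children help build their sampling frame

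*Protocol*

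**What the plan says.** Three places in section 5 of the protocol bear on where controls come from.

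- The opening text of section 5: "cases will be recruited from health facilities and control from the midline household survey". The midline survey takes place once, in November 2014, after round 4.
- Malaria Case Tracker: "cases and controls will be recruited from health facilities", beginning directly after the first administration period.
- Treatment Registers: one purpose of the registers is to "assist with the development of the sampling frame for the control portion of the case-control study". Their content is described thus: "Every child that receives a dose of SP-AQ or SP-AQ + LNS will need to be entered into the treatment register before administration".

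On exposure, the Malaria Case Tracker section states: "The assessed exposure is whether the children received SMC, SMC and nutrition products, or neither". On numbers, it requires 326 cases and adds that "controls will be selected at a ratio of 4 controls:1 case, meaning we will select 1,304 controls".

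A control must have been 6-24 months old in July 2014, with no fever in the past four weeks and no facility care for fever or malaria symptoms since the start of July. Table 7 gives the tracker's location as both health facility and community.

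**The concern.** In a case-control study the controls supply the exposure odds against which the cases are compared. Children in a November household sample, children attending a facility from the first round onward, and children on a list of those dosed can have quite different exposure odds. The H-3 odds ratio therefore depends on which sentence the field team follows. H-3 is one of the three primary hypotheses, and controls recruited from the wrong frame cannot be put right in the analysis.

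The register raises a specific problem. One of the three exposure levels is neither treatment, and a list of children who received a dose does not contain them. The more it is relied on, the fewer untreated controls there are and the more protective treatment appears.

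It is also unclear whether the midline survey, if it is the source, yields as many controls as the protocol states.

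**Working it through.** **1. The passages side by side.**

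| Place in section 5 | Control source | When |
|---|---|---|
| Opening text | Midline household survey | November 2014, once |
| Malaria Case Tracker | Health facilities | From the end of round 1 |
| Treatment Registers | Registers assist with the frame | Books collected after round 4 |

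The first two rows cannot both hold. Table 7's double location fits facility cases with community controls, but it would also fit a mixture, so it does not settle the question.

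Facility controls would also be a narrow group. They must be attending a facility without having sought facility care for fever or malaria symptoms since July. Children attending for other reasons remain possible.

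The household survey does not need the register. Its sample comes from census enumeration areas with a fresh listing of eligible households, whether or not the children were treated.

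**2. How much a partial register frame could matter (illustration).** Assumptions: the protocol's coverage of about 60% means any treatment, there is no true effect, and a share f of controls is drawn from the register.

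- Exposure odds in cases: 0.6/0.4 = 1.5.
- Exposure in controls: 0.6 + 0.4f. Unexposed: 0.4(1 - f).
- Apparent odds ratio: 1.5 × 0.4(1 - f)/(0.6 + 0.4f) = 0.6(1 - f)/(0.6 + 0.4f).

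| f | Apparent odds ratio, treated versus neither |
|---|---|
| 0 | 1.00 |
| 0.10 | 0.54/0.64 = 0.84 |
| 2/7 (29%) | 0.60 |
| 0.50 | 0.30/0.80 = 0.375 |

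The value 0.6 is the protocol's detectable odds ratio. The protocol does not state f, so these figures show sensitivity and are not an estimate of the bias.

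**3. The protocol's sample size reproduced.** Inputs from the Malaria Case Tracker section: control exposure 0.60, odds ratio 0.6, alpha 5% (taken as two-sided), power 90%.

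- Exposure in cases: 0.6 × 0.6/(0.4 + 0.6 × 0.6) = 0.36/0.76 = 0.4737. The mean of the two proportions is 0.5368.
- Cases at 1:1, no continuity correction: [1.960√(2 × 0.5368 × 0.4632) + 1.282√(0.4737 × 0.5263 + 0.6 × 0.4)]² / (0.6 - 0.4737)² = 325.4, rounded up to 326.

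This matches the stated 326. The same calculation at 4:1 needs 203 cases and 812 controls. So 326 is the 1:1 number, and 1,304 = 4 × 326 is added on top of it.

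**4. Yield of the midline survey.** Inputs: 1,500 households, each with at least one child aged 6-28 months, and questions asked about all eligible children. Ages 6-24 months in July become about 10-28 months in November. With ages spread evenly (assumption), the share of control age is 18/22 on an interval count or 19/23 on a count of month classes.

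At one child per household (assumption): 1,500 × 18/22 = 1,227, or 1,500 × 19/23 = 1,239. Both fall below 1,304 before any fever or care-seeking exclusion.

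Using 19/23, the share that must pass both exclusions is 1,304/(1,500 × m × 19/23):

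| Children per household, m (assumption) | Of control age | Share that must pass |
|---|---|---|
| 1.0 | 1,239 | 105% (not reachable) |
| 1.2 | 1,487 | 88% |
| 1.5 | 1,859 | 70% |
| 2.0 | 2,478 | 53% |

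The protocol gives neither m nor the pass share.

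**5. What a shortfall costs.** Power with 326 cases under the protocol's own inputs is below. The last column divides the number of controls by 1.5, the design effect the protocol uses for its surveys. Applying it to controls is an assumption.

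| Controls | Power | With design effect 1.5 on controls |
|---|---|---|
| 326 | 90% | 83% |
| 652 | 96% | 93% |
| 1,304 | 98% | 97% |

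**The case against.** The strongest reply is that the facility sentence is a drafting slip. The opening of section 5 separates the two sources clearly, Table 7 mentions the community, and health workers are said to be trained on the eligibility of cases, with nothing about controls. That makes the survey the likelier intention, but the facility sentence still stands and gives an explicit start time, so the text needs correcting.

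A reader might infer that the register is a third full source and that controls would therefore all be exposed. The protocol does not say that. The register only assists, and Phase 2 of section 4 also lists homes with an under-five child, so the register could supplement a list that includes untreated children. Nor does it remove either level of the contrast for which the study is sized, SMC + LNS versus SMC, because both appear in it. What remains is an undefined role for a list that omits one exposure level.

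A reader might also infer that the survey cannot deliver 1,304 controls. That depends on children per household and on the pass share, neither of which is in the protocol. The protocol calls 750 households per arm a minimum, offers the 4:1 ratio as a way to raise power, and accepts that the estimated sample size may not be reached. All of this stands, so yield is a secondary matter.

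Lastly, using the survey alone brings its own difficulty. A case in August may have had the chance of only one round, while a November control could have had four. If exposure means ever treated, control exposure is inflated in the same direction as with the register. This objection is sound and the fix must deal with it.

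**Conclusion.** The contradiction over the place and timing of control recruitment is established from the text and needs no assumption. It leaves the control group for a primary hypothesis undefined.

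The register problem is conditional. To the extent that controls are drawn from a list of dosed children, the neither group is under-represented and treated-versus-neither odds ratios move toward protection. In the illustration, with 60% coverage by any treatment and no true effect, a share of about 29% is enough to produce an odds ratio of 0.6. The protocol does not show how large the share would be.

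Yield is uncertain. About 1,230 to 1,240 children are of control age at one per household, too few for 1,304. The number becomes reachable at about 1.5 per household with about 70% passing, or 2.0 with 53% passing. A shortfall would not by itself break the stated 90% power, which 326 controls already give before any allowance for clustering. The main harm is selection bias and an undefined control group, not loss of power.

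**What to change.** 1. Name the midline household sample as the only control source. Its enumeration-area listing includes untreated children.
2. Delete the words on controls from the facility sentence in the Malaria Case Tracker section, and align the data-collection text there, so that facilities recruit cases only.
3. In the Treatment Registers section, drop the role in the control sampling frame and limit the register to verifying doses and dates.
4. Define exposure up to comparable reference dates for cases and controls, using the administration dates on the treatment cards, so that November controls are not credited with rounds that an August case could not yet have received.
5. State 1,304 as a target, not a fixed number. Give the assumed children per household and pass share behind it, and say that 326 is the 1:1 requirement before any allowance for survey clustering.

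The cost is mainly protocol wording, plus recording or extracting dose dates that the treatment cards are already meant to carry. No extra recruitment is needed.
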